# Design of a randomized controlled trial of a partnership-based, needs-tailored self-management support intervention for post-treatment breast cancer survivors

**DOI:** 10.1186/s12885-020-06861-x

**Published:** 2020-05-01

**Keywords:** Breast cancer, Randomized controlled trial, Self-management, Empowerment, Self-efficacy, Health-related quality of life

## Abstract

**Background:**

Self-management is becoming essential for breast cancer survivors, but evidence about the effectiveness of self-management support (SMS) intervention is lacking. To address this issue, we developed a theory-based SMS intervention, the ‘EMPOWER’, aimed at empowering breast cancer survivors. Here we describe the rationale of the intervention and its development.

**Methods:**

The conceptual framework of this study is the Chronic Care Model, which posits that SMS can influence patient-provider relationships and ultimately improve health outcomes. We will conduct a multi-center, 2-armed randomized controlled trial to assess the effectiveness of EMPOWER among post-treatment breast cancer survivors in South Korea. The trial will include 94 women who completed primary breast cancer treatment within the last 6 months. Participants will be randomly assigned to the intervention group or the wait-list control group (1:1). The intervention group will receive a 7-week partnership-based and needs-tailored SMS intervention via telephone counseling. The primary outcome is empowerment. The secondary outcomes include self-efficacy for post-treatment self-management behaviors, mental adjustment, psychological distress, and health-related quality of life (HRQOL). Data will be collected by self-reported questionnaire at baseline, post-intervention, and 3-month follow-up.

**Discussion:**

We believe that the EMPOWER intervention could improve HRQOL of post-treatment breast cancer survivors by enhancing their empowerment. If found successful, it could aid clinicians engaged in the long-term care of breast cancer survivors.

**Trial registration:**

Clinical Research Information Service, KCT0004794. Registered 5 March 2020.

## Background

Breast cancer is one of most common cancers among women worldwide. Due to advances in early detection and treatment, approximately 90% of women with breast cancer survive at least 5 years after diagnosis [1]. At some point after treatment, breast cancer may be considered a chronic illness [2].

Breast cancer survivors (BCS) face the numerous health challenges that are associated with a complex chronic condition, including managing persisting symptoms, identifying signs and symptoms of progression, accessing needed information and support, and making healthy lifestyle changes [3, 4]. Shouldering the responsibility for self-management (SM) behaviors can help survivors live well [5]. Unfortunately, cancer survivors in general report feelings of vulnerability and often lack the confidence to initiate the actions required to recover after their treatment [6]. This has led to increasing calls for better SM enablement.

The Chronic Care Model (CCM) is one suggested model for cancer survivorship care [7]. Introduced by Wagner and colleagues [8] in 1998, it was designed to improve the management and health outcomes of individuals with chronic illnesses. In the CCM, the essential element of good care is a productive interaction between informed, motivated patients and a prepared practice team [8]. This interaction can be influenced by 6 components of the CCM [the health system, community resources, self-management support (SMS), delivery system design, decision support, and clinical information systems]. Of those 6 components, SMS has been featured as a key component for assuring quality healthcare [9].

SMS refers to support of an individual’s ability to manage the symptoms, treatment, and physical, psychosocial, and lifestyle changes inherent in living with a chronic condition [8]. The application of SMS intervention among cancer survivors is increasing, and several BCS studies report its efficacy for health outcomes [10–15]. Types of SMS interventions are various and include distress management [10], uncertainty management [11–13], coping [14], and lifestyle management [15]. SMS interventions can significantly improve cancer knowledge [12, 13], cognitive reframing [11–13], self-efficacy [10, 15], and health-related quality of life (HRQOL) [15], and it can decrease psychological distress [10, 11]. Significance has not been demonstrated, however, for SMS effects regarding empowerment [10], patient-provider communication [11, 13], and social support [12], thus rendering the full efficacy of SMS intervention incomplete.

Managing everyday problems brought about by cancer and/or its treatment is likely to be enhanced by a collaborative partnership between patients and health care providers, all of whom are considered co-equal experts of the condition, albeit from different perspectives [16]. Such a collaborative approach can delineate how health care providers can support patients in their SM behaviors [6]. Given the importance of a productive interaction between patients and health care providers in chronic care, an evaluation of relationship-related outcomes such as empowerment is necessary.

In addition, the ‘one-size fits all’ approach for chronic disease SM may not be adequate for a chronic illness as complex as cancer. Several studies have shown that current healthcare systems do not meet the survivors’ needs [17, 18]. Many experts suggest that an individualized or tailored approach should be adopted in survivorship care planning [19]. Because, to the best of our knowledge, few studies have incorporated needs-tailored SMS intervention among BCS, we developed EMPOWER (Partn**E**rship-based, tailored self-**M**anagement support **P**rogram f**O**r **W**omen with breast canc**ER**)—a partnership-based, needs-tailored SMS intervention for BCS who completed their primary treatment. The goal of EMPOWER is to enhance empowerment and increase self-efficacy for SM behaviors, thereby improving health outcomes among post-treatment BCS. This paper describes the design and methodological plan for a randomized controlled trial (RCT) to evaluate the effectiveness of EMPOWER in post-treatment BCS.

### Hypotheses of the EMPOWER trial

The objective of this RCT is to test whether the EMPOWER intervention is effective, compared with a control group, in improving health outcomes (mental adjustment, psychological distress, and HRQOL) by enhancing empowerment and increasing self-efficacy for SM behaviors among post-treatment BCS.

## Methods/design

The EMPOWER trial’s study design and its intervention are in in concordance with the guidelines of the Consolidated Standards of Reporting Trials 2010 statement [20] and the standard protocol Items: Recommendations for Interventional Trials (SPIRIT) [21].

### Study design

This study is a 2-armed RCT designed to test the effects of EMPOWER vs a control intervention. A 7-week EMPOWER intervention will be assessed at baseline (T0), 8 weeks (T1), and 20 weeks (T2). Figure 1 shows a flow chart of the RCT; Fig. 2 shows the schedule of enrollment, interventions, and assessments. The study will be undertaken in South Korea’s two university hospitals—Yonsei Medical Center and Inha University Hospital. The Institutional Review Boards of both provided ethical approval. Written informed consent will be obtained from the participants.

**Fig. 1 Fig1:**
[figure not shown]
RCT flow chart. RCT, randomized controlled trial

**Fig. 2 Fig2:**
[figure not shown]
SPIRIT schedule of enrollment, interventions and assessment. HRQOL, health-related quality of life

### Participants of the study

Women will be eligible to participate if they 1) are aged 19 years or more, 2) were diagnosed histologically with breast cancer, 3) were treated with a curative cancer therapy (surgery, chemotherapy, or radiation therapy), 4) completed a primary cancer treatment within the previous 6 months (except for anti-hormone therapy and targeted therapy) 5) had two or more unmet needs in a post-treatment screening test covering 12 items of unmet needs concerning SM behaviors (i.e., follow-up visit, pain management, fatigue management, insomnia management, lymphedema management, exercise, diet, smoking cessation, alcohol consumption, stress management, return to work, and sexual activity), and 6) are able to use the telephone. Women will be excluded if they had a recurrence, a metastasis, or another cancer.

### Setting and procedure

Potential participants will be identified through physician-referral and self-referral. Physicians ([name], [name] and [name]) will use electronic medical records (EMRs) to screen them for eligibility criteria related to diagnosis and treatment history and will tell potentially eligible women about the study. The researcher ([name]) will screen for more detailed eligibility criteria among women who are interested in participating in the study. Women who learned of our study through a flyer and are interested in participating can contact the researcher ([name]), who will screen them for eligibility via a telephone interview and will review medical information in the EMRs. Women who are finally eligible will meet with the researcher, and all participants will meet in the hospital and provide written informed consent.

Data will be collected via a self-reported questionnaire. After randomization, participants will complete the baseline assessment in a face-to-face interview. The researcher will contact participants via telephone 8 and 20 weeks after baseline and encourage them to complete a follow-up questionnaire via letter mail and send it back in an enclosed pre-addressed and stamped return envelope.

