### Randomization

After the baseline assessment, we will use a computer-generated block randomization procedure (block size 4, 6, 8) in a 1:1 allocation ratio to randomize participants to either the EMPOWER group or the control group. Group assignments will be placed in sealed, sequentially numbered envelopes and opened by the participants. The recruiter will thereby be blinded to the study arm assignments of the participants. Because of the social nature of the intervention, however, participants cannot be blinded to the study arm assignments.

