### Statistical analysis

We will describe the characteristics of the study participants using frequency and percentage for categorical variables and means and standard deviations for continuous variables. To compare baseline characteristics between the two groups, we will use independent *t*-tests for normally distributed continuous variables, the Mann-Whitney test for non-parametric variables, and the chi square test for categorical variables. We will use linear mixed models to analyze the efficacy of EMPOWER and Cohen’s d to estimate effect size as large (≥0.80), moderate (0.5–0.79), or small (< 0.50) [39]. Missing data will be handled under the missing-at-random assumption. We will perform all analyses using IBM SPSS Statistics version 25.0 (IBM, Armonk, NY, USA) according to the intention-to-treat principle and consider a *p*-value < 0.05 significant.

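### The article places the baseline assessment both after and before randomization; if it follows an opened allocation envelope, self-reported T0 scores can be contaminated

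*Protocol article*

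**What the plan says.** Two adjacent sections of the protocol article fix the order of baseline and randomization, in opposite directions.

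- *Setting and procedure*: "After randomization, participants will complete the baseline assessment in a face-to-face interview".
- *Randomization*: "After the baseline assessment, we will use a computer-generated block randomization procedure (block size 4, 6, 8) in a 1:1 allocation ratio".

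The surrounding design is stated as follows.

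- Disclosure of allocation (*Randomization*): "Group assignments will be placed in sealed, sequentially numbered envelopes and opened by the participants".
- Blinding (*Randomization*): "participants cannot be blinded to the study arm assignments".
- Mode of measurement (*Setting and procedure*): "Data will be collected via a self-reported questionnaire". This covers the 30-item empowerment scale, which is the primary outcome, and the secondary scales in Table 4.
- Analysis (*Statistical analysis*): "We will use linear mixed models to analyze the efficacy of EMPOWER and Cohen’s d to estimate effect size". How T0 enters the model is not stated.

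The flow chart (Fig. 1) and the SPIRIT schedule (Fig. 2) may show the order, but they are not reproduced in the text available for this review.

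**The concern.** Both statements are current text and they cannot both be followed. This is not a detail left to a fuller document, because the article states the order twice and the statements disagree.

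The order is consequential in this design. The arms differ visibly: ten telephone sessions with a nurse against an education book, with the intervention available to controls on request only at the end of the study. A woman who has just learned her arm might rate her empowerment, self-efficacy or distress differently from one who has not. If she answers T0 after opening the envelope, T0 is no longer a pre-allocation measurement. A change-from-baseline or group-by-time contrast would then carry any arm-related shift in T0 in full, and a baseline-adjusted contrast would carry part of it. A woman who withdraws between opening the envelope and T0 would also leave no outcome data, and such losses could differ by arm. A T0 collected in this way cannot be repaired afterwards.

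**Working it through.** **1. Setting the sections side by side.** Three readings are possible.

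| Reading | Order | Arm known at T0? | Consequence |
|---|---|---|---|
| A. *Randomization* followed | T0, then envelope opened | No | T0 is clean |
| B. *Setting and procedure* followed, envelope still sealed | Assignment made, T0, then envelope opened | No | Answers at T0 not affected by knowledge of the arm |
| C. *Setting and procedure* followed, envelope already open | Envelope opened, then T0 | Yes | T0 can be contaminated |

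Only C does harm, and nothing in *Setting and procedure* rules it out.

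**2. The plan's own figure.** *Sample size calculation* gives effect size 0.65, power 0.8, alpha 0.05 and 78 patients. A two-sided two-sample t-test needs 38.14 per arm, rounded up to 39, so 2 × 39 = 78, which matches. The normal approximation gives 38 per arm (76). A one-sided test gives 30 per arm and does not match. The figure of 78 does not depend on the order of procedures.

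**3. Illustrative size under reading C.** Let s be the difference in reported T0 (intervention minus control, in SD units) caused only by knowing the arm, with follow-up scores otherwise unaffected. Let b be the slope of follow-up on T0.

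- Change-from-baseline contrast: bias = −s.
- Baseline-adjusted contrast: bias = −b × s.
- Contrast of T1 or T2 levels that does not use T0: bias = 0 from this source.

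Assumptions: the absolute value of s is 0.1 to 0.3, which has no source in the documents. The slope b is 0.69, borrowed from the scale's test-retest reliability in Table 4; that is not a correlation between T0 and week 8 or week 20 in this trial.

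| Absolute s | Change contrast | Share of 0.65 | Adjusted contrast | Share of 0.65 |
|---|---|---|---|---|
| 0.1 | 0.10 SD | 0.10/0.65 = 15% | 0.69 × 0.1 = 0.07 SD | 0.069/0.65 = 11% |
| 0.3 | 0.30 SD | 0.30/0.65 = 46% | 0.69 × 0.3 = 0.21 SD | 0.207/0.65 = 32% |
| 0 | 0 | 0 | 0 | 0 |

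**4. Effect on type I error, same assumptions, 39 per arm.** The standard error is the residual SD × √(2/39), and √(2/39) = 0.226.

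- Adjusted: residual SD = √(1 − 0.69²) = 0.724. The two-sided error is about 0.07 at s = 0.1 and 0.24 at s = 0.3, against a nominal 0.05.
- Change score: residual SD = √(2 × (1 − 0.69)) = 0.787. The error is about 0.09 at s = 0.1 and 0.39 at s = 0.3.

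**5. Direction.** With a true effect of 0.65 and a change contrast, s = +0.3 gives an expected estimate of 0.65 − 0.30 = 0.35, and s = −0.3 gives 0.65 + 0.30 = 0.95. A higher reported T0 in the intervention arm shrinks the effect; a lower one inflates it.

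**The case against.** The strongest reply is that the harmful sequence is stated in neither section. *Setting and procedure* mentions no allocation envelope. The envelope appears only in *Randomization*, and there it comes after baseline. *Randomization* is the dedicated section and gives the sound order, so a one-sentence drafting slip is at least as plausible as a flawed design. This stands as a reason not to claim that the trial will be biased. It does not remove the contradiction, because the sentence that staff would read for the visit procedure still says the opposite.

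Several stronger readings are tempting, and the documents do not support them.

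- *The treatment effect is biased, probably towards the null.* The size and sign of any shift are unknown. Pleased intervention women and disappointed controls would give attenuation, but that is conjecture. The article also does not say how T0 enters the mixed model.
- *Intention-to-treat is defeated.* The article keeps that principle and assumes data missing at random. Even in the sound order, a woman who leaves on learning her arm supplies T0 only, which says little about the effect at T1 or T2. The order matters here, but modestly.
- *The recruiter is unblinded.* The article does not say that the recruiter conducts the baseline assessment.
- *The baseline table becomes meaningless.* Demographic, diagnostic and treatment variables cannot change when a woman learns her arm; only the subjective scores could.
- *T0 answers are given orally to an interviewer.* The abstract and *Setting and procedure* both describe self-reported questionnaires, so the face-to-face interview may simply mean an in-person meeting.

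**Conclusion.** The point holds as an explicit contradiction that is wrong as written and should be corrected. If the order in *Setting and procedure* were followed with the envelope already opened, T0 for the primary and every secondary outcome could be a post-allocation, unblinded self-report. That can bias contrasts that use T0 and can permit arm-dependent withdrawal before any data exist.

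Confidence is high for the contradiction. The bias is conditional on three things: allocation is known at T0, that knowledge changes the answers, and the analysis uses T0. The figures of 0.10 to 0.30 SD (change) and 0.07 to 0.21 SD (adjusted) show what an assumed shift would do against the planned 0.65. They are not estimates for this trial.

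**What to change.** Rewrite the sentence in *Setting and procedure* to agree with *Randomization*: written consent, then the T0 questionnaire completed, then the next numbered envelope opened. Add that the envelope is released only once a completed T0 questionnaire is in hand. Check that Fig. 1, Fig. 2 and the site instructions show the same order.

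The cost is one sentence in the protocol and the matching line in the site instructions. Consent is already given in the hospital and baseline is already in person, so an extra visit should not be needed; the article does not say where the envelope is opened, so the instruction should state this. The 78 evaluable patients are unaffected, and with T0 completed before disclosure this source of bias is zero.

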### Randomization

After the baseline assessment, we will use a computer-generated block randomization procedure (block size 4, 6, 8) in a 1:1 allocation ratio to randomize participants to either the EMPOWER group or the control group. Group assignments will be placed in sealed, sequentially numbered envelopes and opened by the participants. The recruiter will thereby be blinded to the study arm assignments of the participants. Because of the social nature of the intervention, however, participants cannot be blinded to the study arm assignments.

### Study groups

#### The EMPOWER intervention group

Based on the CCM, EMPOWER involves provider-participant partnerships. Such partnerships that help participants play a larger role in managing their post-treatment medical problems, thereby helping them reach their care goals [7]. SMS empowerment can extend to late and long-term treatment effects as well, helping survivors understand when to seek support and encouraging healthy lifestyle changes [6].

Participants in the EMPOWER group will receive a 7-week partnership-based, needs-tailored SMS intervention via telephone counseling (ten 15- to 20-min sessions, totaling 175 min). We extracted the intervention program contents from the conceptual SM framework in chronic illness [22], the qualitative data from a Korean BCS focus group interview regarding post-treatment SM needs [23] structured by 5 SM tasks (medical management, symptom management, lifestyle management, emotional management, and role management) and 21 specific topics (Table 1). An expert advisory team (3 surgeons, 1 advanced practice nurse, and 1 nursing professor) validated the final thematic structure.

**Table 1 Tab1:** Thematic structure and contents of the EMPOWER intervention

SM task	SM education topic	SM skill training
Medical management	Follow-up after treatment	
	Late/long-term effects	
	Sign and symptoms of recurrence	
	Second cancer screening	
	Vaccination	
	Side effects of anti-hormone therapy (if applicable)	
Symptom management	Pain	√
	Peripheral neuropathy	
	Fatigue	√
	Insomnia	√
	Lymphedema	
Lifestyle management	Exercise	√
	Diet	√
	Smoking cessation	
	Alcohol restriction	
	Weight control	
Emotional management	Distress	√
Role management	Body image	
	Sexuality (if applicable)	
	Return to work (if applicable)	
	Recovery of self-confidence	

*SM* self-management

The EMPOWER intervention is subdivided into a 3-week SM education part and a 4-week SM skill training part (Table 2). At the end of the education part, participants will receive SM skill training in the topic of their choice. Currently, we have modules for the 6 topics (pain, fatigue, insomnia, exercise, diet, and distress) we have accumulated evidence for the intervention. Through participant choice, providers can tailor SM skill training to individual needs.

**Table 2 Tab2:** Delivery of the EMPOWER intervention

Week	Session no.	Topic	Telephone time (min.)
1	1	SM education: Medical management	20
	2	SM education: Symptom management	20
2	3	SM education: Lifestyle management	20
	4	SM education: Emotional management	20
3	5	SM education: Role management	20
	6	1st SM skill training: Selected own topic	15
4	7	2nd SM skill training: Selected own topic	15
5	8	3rd SM skill training: Selected own topic	15
6	9	4th SM skill training: Selected own topic	15
7	10	Discussion: Healthy future plan	15
		Total	175

Using a 96-page evidence- and theory-based workbook, master-level nurses will deliver the SM education and skill training by telephone. The education and action planning contents of the workbook were extracted from the Korean National Cancer Information Center [24], the National Comprehensive Cancer Network [25], and the Oncology Nursing Society [26]. During the education sessions, providers will exploit Badura’s self-efficacy sources [27], such as verbal persuasion, vicarious experience, mastery, and physiological states. The workbook, for example, includes various vicarious experiences leading, for example, to success in weight management, exercise performance, and work resumption. During the SM skill training sessions, providers will present Lorig and Holman’s SM skills of problem solving, decision-making, taking action, forming partnerships, and utilizing resources [22]. The training uses a structured module according to a weekly plan (Table 3). The participant workbook is composed of a structured format that includes problem identification, goal setting, action planning, resource identification, and action monitoring. Facilitation of provider-participant partnerships is provided by a telephone counseling module that uses motivational interviewing principles (i.e., open questions, affirmation, reflective listening, and summary reflections) [28].

**Table 3 Tab3:** Weekly contents of 6 self-management skill training modules

Module	Goal	Week 1	Week 2	Week 3	Week 4	Week 5
Pain	Able to verbally express own pain and practice according to pain Mx plan.	Weekly goal: Understand the pattern of pain (severity, location, quality, duration, etc.). Action plan: Making a pain diary	Weekly goal: Learn ways of pain Mx based on each pain type. Action plan: Making a pain diary.	Weekly goal: Practice pain Mx plan. Action plan: Making a pain diary.	Weekly goal: Practice pain Mx plan. Action plan: Making a pain diary.	Weekly goal: Plan future life.
Fatigue	Able to identify the cause of own fatigue and practice according to fatigue Mx plan.	Weekly goal: Identify the cause and pattern of fatigue. Action plan: Self-assessment of fatigue.	Weekly goal: Learn ways of fatigue Mx. Action plan: Making a fatigue diary.	Weekly goal: Practice fatigue Mx plan. Action plan: Making a fatigue diary.	Weekly goal: Practice fatigue Mx plan Action plan: Making a fatigue diary.	Weekly goal: Plan future life.
Insomnia	Able to identify pattern of own insomnia and practice according to insomnia Mx plan.	Weekly goal: Identify insomnia pattern. Action plan: Making a sleep diary.	Weekly goal: Learn ways of insomnia Mx (stimulation control). Action plan: Making a sleep diary.	Weekly goal: Practice insomnia Mx plan. Action plan: Making a sleep diary.	Weekly goal: Practice insomnia Mx plan. Action plan: Making a sleep diary.	Weekly goal: Plan future life.
Exercise	Able to establish individualized exercise goal and practice according to exercise plan.	Weekly goal: Understand 4 elements of exercise (frequency, intensity, timing, type). Action plan: Making an exercise contract.	Weekly goal: Establish individualized exercise goal. Action plan: Making an exercise diary.	Weekly goal: Practice the exercise plan. Action plan: Making an exercise diary.	Weekly goal: Practice the exercise plan. Action plan: Making an exercise diary.	Weekly goal: Plan future life.
Diet	Able to establish individualized diet goal and practice according to diet plan.	Weekly goal: Understand importance of balanced diet. Action plan: Making a diet contract.	Weekly goal: Establish individualized diet goal. Action plan: Making a diet diary.	Weekly goal: Practice diet plan. Action plan: Making a diet diary.	Weekly goal: Practice diet plan. Action plan: Making a diet diary.	Weekly goal: Plan future life.
Distress	Able to identify types of distress and practice according to emotional Mx plan.	Weekly goal: Identify level, cause, type of distress. Action plan: Completing NCCN distress thermometer.	Weekly goal: Learn ways of emotional Mx. Action plan: - Anxiety: Practicing abdominal breathing - Depression: Exercise or meditation (preferred)	Weekly goal: Practice emotional Mx plan. Action plan: - Anxiety: Practicing abdominal breathing - Depression: Exercise or meditation (preferred)	Weekly goal: Practice emotional Mx plan. Action plan: - Anxiety: Practicing abdominal breathing - Depression: Exercise or meditation (preferred)	Weekly goal: Plan future life

*Mx* management, *NCCN* National Comprehensive Cancer Network

